## LIST OF ABBREVIATIONS AND RELEVANT DEFINITIONS

|                       |                                                                                                                         |
|-----------------------|-------------------------------------------------------------------------------------------------------------------------|
| ACC            | Anterior Cingulate Cortex                                                                                               |
| AE             | Adverse Event                                                                                                           |
| AR             | Adverse Reaction                                                                                                        |
| BOLD           | Blood Oxygen Level Dependent Imaging                                                                                    |
| CA             | Competent Authority                                                                                                     |
| CB1/2          | Cannabinoid-binding receptors 1 and 2                                                                                   |
| CBD            | Cannabidiol (cannabinoid)                                                                                               |
| CCMO           | Central Committee on Research Involving Human Subjects; in Dutch: Centrale Commissie Mensgebonden Onderzoek             |
| CBM            | Cannabinoid-based Medicine                                                                                              |
| CV             | Curriculum Vitae                                                                                                        |
| CSI            | Central sensitization index                                                                                             |
| DN-4           | Douleur Neuropathique 4                                                                                                 |
| DSMB           | Data Safety Monitoring Board                                                                                            |
| EB             | Epidermolysis Bullosa                                                                                                   |
| EU             | European Union                                                                                                          |
| EudraCT        | European drug regulatory affairs Clinical Trials                                                                        |
| fMRI
(BOLD) | Functional Magnetic Resonance Imaging (Blood Oxygen Level Dependent)                                                    |
| GCP            | Good Clinical Practice                                                                                                  |
| GDPR           | General Data Protection Regulation; in Dutch: Algemene Verordening Gegevensbescherming (AVG)                            |
| HADS           | Hospital anxiety and depression survey                                                                                  |
| IB             | Investigator's Brochure                                                                                                 |
| IC             | Informed Consent                                                                                                        |
| IMP            | Investigational Medicinal Product                                                                                       |
| IMPD           | Investigational Medicinal Product Dossier                                                                               |
| METC           | Medical research ethics committee (MREC); in Dutch: medisch-ethische toetsingscommissie (METC)                          |
| SF-MPQ2        | Short-form McGill Pain Questionnaire 2                                                                                  |
| PCS            | Pain catastrophizing scale                                                                                              |
| PSEQ           | Pain self efficacy questionnaire                                                                                        |
| (S)AE          | (Serious) Adverse Event                                                                                                 |
| SPC            | Summary of Product Characteristics; in Dutch: officiële productinformatie IB1-tekst                                     |
| Sponsor        | The sponsor is the party that commissions the organisation or performance of the research, for example a pharmaceutical |

company, academic hospital, scientific organisation or investigator. A party that provides funding for a study but does not commission it is not regarded as the sponsor, but referred to as a subsidising party.

|              |                                                                                                            |
|--------------|------------------------------------------------------------------------------------------------------------|
| SUSAR | Suspected Unexpected Serious Adverse Reaction                                                              |
| THC   | Delta-9-Tetrahydrocannabinol (cannabinoid)                                                                 |
| UAVG  | Dutch Act on Implementation of the General Data Protection Regulation; in Dutch: Uitvoeringswet AVG        |
| WMO   | Medical Research Involving Human Subjects Act; in Dutch: Wet Medisch-wetenschappelijk Onderzoek met Mensen |

## SUMMARY

**Rationale:** There is an unmet need for more effective pain alleviation in EB patients. EB patient anecdotes on the use of cannabinoid-based medicines (CBMs) are in line with current science aimed at assessing the effectiveness of CBMs for chronic pain conditions. Until now evidence on the effectiveness of CBMs is moderate and is inconclusive. As the pain quality item “unpleasantness” delineates EB pain, we hypothesize the modulation of affective pain processing in the brain by way of intervention with Transvamix (a CBM comprising THC and CBD) - objectified by functional magnetic resonance imaging (fMRI).

**Objective:** The primary objective is to determine the effect of Transvamix on the pain quality item “unpleasantness”, relative to placebo. Secondary objectives include the assessment of general pain qualities, pain self-efficacy, general pain and pruritus intensity, functional brain connectivity, adverse events and sub-side effect threshold maintenance dose achieved during titration.

**Study design:** The study is a two-arm, randomized, double-blind, placebo controlled, crossover intervention study.

**Study population:** Sixteen mentally competent patients with EB, 16 years or older, registered at the Centre for Blistering Diseases (department of Dermatology, UMCG) with a genetic diagnosis of EB – and an average pain score >3 on a numeric rating scale (NRS 0-10).

**Intervention:** Transvamix-oil comprising 100mg/mL THC and 50mg/mL CBD (10% THC / 5% CBD), and placebo, to be administered sublingually by a 1mL dosing syringe.

**Main study parameters/endpoints:** The effect of Transvamix, relative to placebo measured by a reduction in the pain quality items for “unpleasantness” (using the short-form McGill pain questionnaire by 30% and 50%; after 2 weeks of Transvamix and 2 weeks of placebo).

**Nature and extent of the burden and risks associated with participation, benefit and group relatedness:** Currently epidermolysis bullosa patients are using cannabinoid-based medicines both with and without medical supervision. Participants are 16 years or older and mentally competent. They will receive the study intervention Transvamix-oil, a compounded medication (*magistrale bereiding*) readily available on prescription and is currently used by patients for various medical indications in the Netherlands. Transvamix-oil can produce side effects that can be discomforting, but are mild, well tolerated, and disappear within 4-8 hours after administration upon which the following dose can be reduced to mitigate the recurrence of side-effects. Participants will undergo 3x 30 minute MRI scans. A daily logbook will be completed at home electronically - pertaining to the dose administered, possible side-effects and pain/pruritus scores. All participant reported outcomes are completed electronically at home.

### 1.2 Transvamic-oil (cannabinoid-based medicine oil)

Transvamic-oil is produced by the Transvaal pharmacy as a compounded medication (*magistrale bereiding*) and prescribed to patients with refractory symptoms, of which pain is the most prevalent indication. CBM-oil prescriptions have been filled out over 100,000 times to patients in the Netherlands between 2015 and 2020 . Since their appearance on the market 52 adverse events related to sublingually administered CBMs (of which 1 was serious: hypoglycemia) have been reported to the center for pharmacovigilance (LAREB). Activities such as driving vehicles or using dangerous apparatus can be impaired in the acute phase after administering CBMs containing both THC and CBD, such as through delayed reaction times. A recent study highlighted that after a single administration of 13.75mg THC and CBD, which was vaporized and inhaled, the resulting impairments did not exceed 240 minutes. Additionally, a placebo-controlled crossover study using an oromucosal THC:CBD spray in varying compositions, observed the largest decrease in subjective wakefulness at 3 hours post administration.

In general, short-term use of Transvamic-like drugs increases the risk for non-serious adverse events 1.86 times, of which dizziness is the most frequently reported . The side-effect profile however is described as acceptable for clinical practice. Detectable plasma

THC levels after oromucosal absorption are reached at 30-45 minutes and maximum concentration at 2-3 hours. Increasing dose tolerance to therapeutic effects has not been observed in Transvamic-like drugs.

### 1.3 Transvamic & Pain in EB

The use of CBMs as treatments for pain have preceded scientific studies (such as phase I and II studies) whereby great numbers of CBMs have been developed and are prescribed to patients. The consequence is that results from any new pharmacokinetic studies, on single CBM interventions, cannot be accurately applied to other CBMs already existing on the market due to the numerous CBM compositions and administration forms. Thus, researching all CBMs is not feasible.

To date, it has also been shown that neither the dose administered nor detected plasma levels of cannabinoids are good predictors of pain alleviation when treated with CBMs. The high inter-individual variability (CV%) is likely due to patient variations in BMI, enterohepatic circulation, degradation in the gut, previous cannabinoid exposure, the endogenous cannabinoid system (endocannabinoid system) compositions and differences in administration technique. Additionally, the subjective effects after cannabinoid administration do not appear to have a classic monophasic dose-response relationship. One such study observed that higher doses did not lead to improved effectiveness, versus lower doses, in oromucosal cannabinoid preparations (THC & CBD). Another study did however highlight dose-dependent effects on heart rate, after inhaling cannabis (THC), however this dose-dependent relationship was absent for the subjective effects associated with cannabinoid administration. A recent study using vaporised cannabinoids in chronic pain patients with fibromyalgia (Bedrocan: Bediol, Bedrolite, Bedrocan & placebo) clearly showed that after single administration, the subjective changes in evoked pressure pain had a temporal relationship with plasma cannabinoid levels after administration – however only single doses were used in this study. Therefore, the current best-practice is for patients administering CBMs to undergo dose-escalation titration following a premeditated dosage build-up scheme (e.g. administration 4x daily). In order to achieve an effective dose, patients continue titration until side-effects are reached, and subsequently reduce their dose by one step in the titration scheme (table 1), and subsequently maintain this dose. Methods for dose-escalation vary significantly between patients in clinical practice, which is why a fixed titration scheme should be employed for research studies. This feasibly standardizes the dose-escalation for all participants in clinical studies.

Pain however is a multidimensional experience comprising physical (nociceptive) and emotional/psychological (conditioning) components. An additional challenge in EB patients is that most patients suffer from pain caused by multiple physical and pathophysiological aetiologies. A well-known example of this, which has been described in all EB subtypes, is chronic neuropathic pain accompanied by continuous nociceptive pain from chronic wounds and inflammation of the skin or mucosa. Adding further burden is the psychological response (pain affect) to chronic pain that exacerbates and worsens one's experiences of pain. The role of nociplastic pain (pain that arises from altered nociceptive function) has not been investigated in EB, however given its postulated role in chronic pain conditions, may indeed be relevant in EB-related pain. Due to this complex nature of chronic pain in EB, adequate analgesia is not achieved by single pharmacologic interventions, and on the contrary, the side-effect burden of poly-analgesic-pharmacy outweighs the decision to prescribe multiple pharmacologic interventions.

In a recent cross-sectional study on EB in the Netherlands, patients rated 20 qualities of pain. The highest score in all subtypes in the cohort was that for an “unpleasant” quality of pain. This is interesting as research has shown that pain affect, located in the limbic system, which is reported by patients as the pain quality “unpleasantness”, is functionally distinct from sensory pain processing pathways. One way to measure pain affect is using functional magnetic resonance imaging (fMRI) techniques to measure brain connectivity in known and suspected areas processing pain affect. Numerous studies using this technique have identified the amygdala and anterior cingulate cortex (ACC) as central brain areas that alter connectivity during chronic pain. Furthermore, independent of the aetiology of chronic pain, all chronic pain states (measured by fMRI) show similarities in altered brain connectivity, which are subsequently reversed (improved) with successful treatments.

Endogenously produced cannabinoids (endocannabinoids) play a key role in the modulation of pain signals by binding endocannabinoid receptors 1 and 2 (CB1/2). CB1/2 are ubiquitous, most prevalently found in the central and peripheral nervous systems, however are sparsely distributed in lower brain-stem regions for cardiovascular and respiratory functions, which explains the unattainable lethal doses and complete absence of mortality from plant derived CBMs. As CB1/2 are densely populated in the frontal-limbic areas of the brain, their role modulating pain affect has been proposed. Like these endocannabinoids, exogenous cannabinoids (CBMs), namely THC and CBD, also target these receptors; modulating neurotransmitter release in the CNS. Specifically, the amygdala and ACC are shown to have altered functional connectivity to brain cortices through CB1/2 agonism. This change in connectivity significantly correlates with a decrease in the pain, and

more specifically a decrease in the pain quality “unpleasantness” from noxious stimuli after systemic administration of TransvamiX-like drugs (comprising THC and CBD) . Generally, in clinical studies for a heterogeneous group of chronic pain conditions, moderate evidence was shown for the efficacy of CBMs versus placebo . In addition to this, in recent years, clinical studies on various painful diseases have shown the superiority of combining multiple cannabinoids compared to single-cannabinoid extracts, with specific regard to the combination of THC & CBD . Which is also attributed to an improved tolerance of CBM interventions when both THC and CBD are combined, whereby higher doses can be administered .

#### 1.4 Concluding Remarks

Taken together, the unmet symptomatic treatment needs in EB and moderate quality evidence for the use of TransvamiX-like drugs to treat pain and modulate pain affect, open up grounds for further clinical investigation.

New fMRI techniques to assess brain connectivity will objectify both baseline characteristics in connectivity in EB patients with pain, as well as connectivity changes in areas processing pain affect. As we employ standardized dose-escalation schemes, a pharmaceutical grade CBM intervention, validated patient reported outcomes, and a sufficient sample size, we will be able to use rigorous statistical analyses and shed light on TransvamiX effects on chronic pain in EB. We hypothesize a novel avenue of pain intervention for EB with regard to modulating pain affect – objectified by fMRI.

## **2. OBJECTIVES**

### **2.1 Hypothesis:**

- CBM-oil comprising both THC and CBD (Transvamix 10% THC / 5% CBD) can alleviate pain in patients with inherited epidermolysis bullosa.

### **2.2 Primary Objective**

- To determine the effect of Transvamix, relative to placebo, on participant reported pain scores of the quality “unpleasantness” in EB patients with chronic pain.

### **2.3 Secondary Objectives**

- To explore the effect of Transvamix, relative to placebo, on participant reported general pain quality scores, and pain intensity, in EB patients with chronic pain.
- To explore the effect of Transvamix, relative to placebo, on pain self-efficacy in EB patients with chronic pain.
- To explore the effect of Transvamix, relative to placebo on pruritus intensity in EB patients with chronic pain.
- To explore the effect of Transvamix, relative to placebo on brain connectivity in areas corresponding to the affective pain modulation circuit.
- To determine the sub-side effect threshold maintenance dose achieved during titration of Transvamix and placebo.
- To determine the frequency and participant-reported burden of adverse-events encountered during titration of Transvamix and placebo.

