## 6.6 Dosages, dosage modifications and method of administration

Transvamic and placebo are administered sublingually using a 1 millilitre dosing syringe. All participants will follow the predetermined titration scheme (*Table 2*). The titration will be stopped at the onset of side-effects (as reported by the participant), and the dose administered reduced by one day in the titration scheme. This will be called the sub-side effect threshold maintenance dose.

This achieved dose will be maintained for the remaining intervention period until day 14 is completed for each intervention (Transvamic and placebo). Both placebo and IMP (Transvamic) will undergo the same titration scheme.

The maximum dose is 0.75ml/day Transvamic or placebo (divided between 4 separate administrations).

For additional information please see *D1\_Investigators Brochure* chapter 5.3.1.

| Table 2: Titration Scheme                                 |           |          |           |            | Total   | Total THC | Total CBD |
|------------------------------------------------------------------|-----------|----------|-----------|------------|---------|-----------|-----------|
| Transvamic (100mg/mL THC & 50mg/mL CBD) & Placebo |           |          |           |            | (ml)    | (mg)      | (mg)      |
| Day                                                              | 6AM – 9AM | 11AM-2PM | 4PM – 7PM | 9PM – 12AM |         |           |           |
| 1                                                                | -         | -        | -         | 0,05 ml    | 0,05 ml | 5         | 2,5       |
| 2                                                                | -         | -        | -         | 0,05 ml    | 0,05 ml | 5         | 2,5       |
| 3                                                                | 0,05 ml   | -        | -         | 0,05 ml    | 0,1 ml  | 10        | 5         |
| 4                                                                | 0,05 ml   | -        | 0,05 ml   | 0,05 ml    | 0,15 ml | 15        | 7,5       |

|    |         |         |         |         |         |    |      |
|----|---------|---------|---------|---------|---------|----|------|
| 5  | 0,05 ml | 0,05 ml | 0,05 ml | 0,05 ml | 0,2 ml  | 20 | 10   |
| 6  | 0,05 ml | 0,05 ml | 0,05 ml | 0,1 ml  | 0,25 ml | 25 | 12,5 |
| 7  | 0,1 ml  | 0,05 ml | 0,05 ml | 0,1 ml  | 0,3 ml  | 30 | 15   |
| 8  | 0,1 ml  | 0,05 ml | 0,1 ml  | 0,1 ml  | 0,35 ml | 35 | 17,5 |

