#### 8.1.2 Secondary study parameters/endpoints.

- The difference of mean scores of pain qualities between Transvamic and placebo.  
*Will be measured as the difference of the mean of all SF-MPQ2 pain quality items (which have received a score >0 on NRS) between Transvamic and Placebo.*
- The difference of mean scores of pain intensity between Transvamic and placebo.  
*Will be measured as daily changes in pain intensity (1-14 days placebo, 1-14 days Transvamic) using the VAS-Pain ([no pain] 0-100 [worst pain imaginable] unit scale) for pain intensity. The change score (delta) from baseline to Transvamic (day 14) and Placebo (day 14) will be calculated.*
- To determine the effect of Transvamic on pain self-efficacy  
*Will be measured using the PSEQ survey pre-intervention (1x baseline) and during intervention (1x Transvamic, 1x placebo), a 10-item survey on the ability to continue normal life given ongoing pain.*
- The difference of mean scores of pruritus intensity between Transvamic and placebo.  
*Will be measured as daily changes in pruritus intensity (1-14 days placebo, 1-14 days Transvamic) using the VAS-Pruritus ([no pruritus] 0-100 [worst pruritus imaginable] unit scale) for pruritus intensity. The change score (delta) from baseline to Transvamic (day 14) and Placebo (day 14) will be calculated.*
- The difference in brain connectivity of the seed regions (anterior cingulate cortex and amygdala) to the brain cortex between Transvamic and placebo.  
*Will be measured using voxel-based analysis of blood oxygen-level dependent functional magnetic resonance imaging (fMRI-BOLD).*

- To determine sub-side effect threshold maintenance dose achieved of Transvamic during titration and the respective interindividual variability (CV%).  
*Will be measured as the dose administered on day 14 of placebo and Transvamic interventions. CV% is measured as inter-participant variance of dose achieved on day 14 of placebo and Transvamic interventions.*
- To inventorize how many and which participant-experienced adverse-events during titration and maintenance of Transvamic and the patient reported burden for each adverse event on numeric rating scale (NRS [not burdensome at all] 0-10 [extremely burdensome]).

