### 9.2 AEs, SAEs and SUSARs

#### 9.2.1 Adverse events (AEs)

Adverse events are defined as any undesirable experience occurring to a subject during the study, whether or not considered related to Transvamic or placebo. All adverse events reported spontaneously by the subject or observed by the investigator or his staff will be recorded.

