### 10.2 Secondary study parameter(s)

#### 10.2.1 Participant Reported Outcome Measurements (PROMs)

For all PROMs (SF-MPQ2 [all items], PSEQ [all items] and VAS pain/pruritus), descriptive statistics will be employed to portray means and standard deviations or medians and interquartile ranges for the measurements: baseline, placebo and Transvamic. The number of adverse events, and the participant reported burden of each, will be presented for each group (placebo and Transvamic) using frequencies of reported adverse events, means with standard deviations or median with interquartile ranges (depending observed distribution).

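### The adverse-event secondary endpoint has no single window or consistent naming of arms: 2.3 stops at titration, 8.1.2 adds maintenance but names only Transvamix, 10.2.1 gives no window

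*Protocol*

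**What the plan says.** Three sections of the protocol describe this secondary endpoint.

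- Section 2.3 (objective): "To determine the frequency and participant-reported burden of adverse-events encountered during titration of Transvamix and placebo". Both treatments are named, and the window is titration.
- Section 8.1.2 (endpoint): "To inventorize how many and which participant-experienced adverse-events during titration and maintenance of Transvamic and the patient reported burden for each adverse event". The window is titration plus maintenance, and placebo is not named.
- Section 10.2.1 (analysis): the number of events and their burden "will be presented for each group (placebo and Transvamic) using frequencies of reported adverse events". Both treatments are covered, and no window is stated.

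Section 6.6 fixes where titration ends: "The titration will be stopped at the onset of side-effects (as reported by the participant"). The dose then goes back by one day of the scheme and is held to day 14 of that treatment period. Titration and maintenance are therefore separate phases, and the boundary between them is the first side effect.

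Under section 8.3.1 and Table 1, participants record side effects daily in a logbook throughout both treatment periods (days 1 to 14 and 29 to 42), from a 15-item list with a 0 to 10 burden rating.

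**The concern.** Someone writing the analysis could follow 2.3 or 8.1.2 and comply with the protocol either way, yet the two give different numbers from the same logbook.

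The 2.3 version has a particular weakness. Its window closes on the event being counted: a participant with early side effects is observed briefly, and one without any is observed for all 14 days. If Transvamix and placebo differ in when side effects start, they also differ in how long they are observed. Side effects at the maintained dose drop out, although section 13.1(j) says that stepping back in the scheme avoids them. Only data from maintenance can show whether it does. Section 9.5 adds that basic safety and tolerability data for this product are lacking, so the tolerability description has some weight even in an exploratory study.

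**Working it through.** The protocol gives no rate or target for this endpoint, so there is no stated figure to reproduce. The check compares the passages and then works out what the window rule implies.

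**Step 1: the passages side by side**

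| Section | Window | Treatments named |
|---|---|---|
| 2.3 | Titration | Transvamix and placebo |
| 8.1.2 | Titration and maintenance | Transvamix |
| 10.2.1 | None stated | Transvamix and placebo |
| 8.3.1 (data collection) | Every treatment day | Transvamix and placebo |

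The first two rows conflict on window. Section 8.1.2 differs from the other three on treatments.

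**Step 2: how much of a period the titration window covers**

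Let T be the day of the first reported side effect, counted as the last titration day. The titration window has length min(T, 14) days. The uncounted part is 14 − T days when T ≤ 14, and zero when there is no side effect. Over the full period, the number of side-effect days can lie anywhere from 1 (the onset day only) to 1 + (14 − T).

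| Onset day T | Share of period counted | Days left out | Side-effect days, titration only | Side-effect days, full period (possible range) |
|---|---|---|---|---|
| 3 | 3/14 = 21% | 11 | 1 | 1 to 12 |
| 5 | 5/14 = 36% | 9 (64%) | 1 | 1 to 10 |
| 7 | 7/14 = 50% | 7 | 1 | 1 to 8 |
| 10 | 10/14 = 71% | 4 | 1 | 1 to 5 |
| None | 14/14 = 100% | 0 | 0 | 0 |

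The onset days are illustrations; the protocol does not predict them. The ranges are logical limits, not expected values.

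**Step 3: which summaries depend on the window**

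- *Side-effect days.* If m side-effect days occur during maintenance, the titration-only count is 1 and the full-period count is 1 + m. They agree only when m = 0.
- *Number of events.* Several list items can be ticked on the day titration stops, so titration only can still give more than one event. It gives at most one side-effect day per participant per period, and every item ticked later is lost.
- *Burden.* Titration only uses ratings from the stopping day. The full period also includes ratings at the reduced dose.
- *Proportion with at least one side effect.* A participant has one within 14 days exactly when T ≤ 14, and day T lies inside the titration window. This proportion is therefore the same under both windows.

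**The case against.** The best defence is that the protocol uses the word titration loosely for the whole treatment period. The objective just before the quoted one speaks of a maintenance dose achieved during titration, and sections 8.1.2 and 10.2.2 measure that dose at the end of each period. Table 1 labels both periods as titration and maintenance, the logbook runs every day, and 10.2.1 imposes no titration limit. This makes a full-period analysis the likely intention. It does not remove the inconsistency, because 8.1.2 and Table 1 name the two phases separately and 6.6 says when the first one ends. It does rule out the inference that maintenance events will in fact be discarded.

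On arms, a reader might infer from 8.1.2 that there is no placebo comparison. The text does not support that. Other 8.1.2 items also lead with Transvamix alone and then measure both treatments (pain self-efficacy, dose achieved). Sections 2.3, 8.3.1 and 10.2.1 all include placebo. What remains is a wording gap.

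On sources, a reader might infer that 9.2.1 offers a competing version of the endpoint, since it defines an adverse event as "any undesirable experience occurring to a subject during the study, whether or not considered related to Transvamic or placebo". That section is general safety reporting. The endpoint is participant-reported and carries a burden rating, and only the logbook records burden. Nor does 9.2.1 mention burden, so it gives no ground for setting aside effects rated 0.

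On size, it is tempting to take the 1.86 in section 1.2 as a daily rate ratio and conclude that titration-only counting pulls the Transvamix-placebo ratio towards 1. That figure is an increase in risk for similar drugs, not a daily rate in this trial. The calculation would also need a constant daily rate, despite a rising dose followed by a step-down, and it would set a probability of any event against an expected number of event-days. The documents support neither a ratio nor a direction of bias.

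**Conclusion.** The point holds as an inconsistency of window, with a lesser one in the naming of treatments. Taken literally, the window in 2.3 depends on the outcome, can differ in length between Transvamix and placebo, and omits the maintenance phase, which is 9 of 14 days if onset is on day 5. This changes counts of events, side-effect days and burden summaries by an amount the documents do not allow one to estimate. The proportion with any side effect is unchanged. The conclusion assumes that titration stops at the first reported side effect as 6.6 says, and that the onset day counts as titration. Importance is modest: the endpoint is secondary, 10.2.1 plans only descriptive summaries with no test, and the data for the full-period version are already collected.

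**What to change.** Use one definition in 2.3, 8.1.2 and 10.2.1: side effects and their burden as recorded in the daily logbook of 8.3.1, over all 14 days of each treatment period (days 1 to 14 and 29 to 42), covering titration and maintenance, for both Transvamix and placebo. State that events captured under 9.2.1 are reported separately as safety data, since they need not carry a burden rating.

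The cost is a change of wording in three sections. No data collection, dosing rule or sample size is affected. The change should be made before unblinding, so that the choice of window cannot follow the results.
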